### Recruitment

All participants will be recruited in the three hospitals mentioned above through hospital-based advertisements. Once they have volunteered to participate, they will be assessed according to the inclusion and exclusion criteria. Eligible patients will be asked to sign the written informed consent form before intervention begins.

### Randomization, allocation, and blinding

The central randomization method will be performed by the Shanghai University of Traditional Chinese Medicine. Block randomization will be used, and the block size will be unknown to the researchers. The information of patients will be sent by an independent researcher to the center via the hospital’s website. Randomization will be performed automatically under the control of a central computer system. The researcher will be able to get the random numbers and group allocation immediately in the form of an email or short message service. Patients will be randomly divided into four groups with the ratio of 1:1:1:1.

This is a patient-blinded trial, based on treatment allocation. Physicians who prescribe the study medication and acupuncture therapy will not be involved in the outcome assessments or data analyses. All the outcome assessors and statisticians are blinded to the group assignment. Patients will wear an eye-mask during the acupuncture treatment, and each acupuncture treatment will be carried out in an enclosed space to ensure the successful implementation of the blinding method. Researchers will accept the training of the specifications of this study and be asked to adhere strictly to the principle of task separation.

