### Quality control

To ensure the quality of the trial, it will be conducted at three hospitals, and the trial data will be input on the ResMan website in a timely manner. The Clinical Research Center of Drugs of the Shanghai Municipal Hospital of Traditional Chinese Medicine will work as the data monitoring team to identify the existing problems in the project, control the bias, and make the final decision to terminate the trial. A qualified clinical trial expert will be invited to monitor this RCT. Researchers will be trained to ensure the quality of the cognitive tests. Acupuncturists participating in this trial are all certificated physicians with 3–5 years of clinical experience. To ensure that the acupuncture and sham acupuncture treatment are performed uniformly across the three hospitals, we will carry out centralized trainings twice for these acupuncturists before the trial begins.

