### Statistical analysis

An intention-to-treat (ITT) analysis will be used in this RCT. Data analyses will be performed with the use of the statistical software SPSS20.0. The baseline characteristics of the participants in the four groups will be dealt with using the chi-squared test and Fisher Exact Test for categorical data and analysis of variance for continuous variables. Intragroup comparisons will be performed via the use of paired *t* test. The main effect and the interaction effect of the two interventions will be analyzed by 2 × 2 factorial analysis of variance. The statistical significance is set at *P* < .05. All the *P* values are two-side.

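### Three hospitals recruit, but no stratification of the blocks by hospital is stated and the stated 2 × 2 ANOVA has no hospital factor, so precision may be lost

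*Protocol article*

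**What the plan says.** The Randomization, allocation, and blinding section assigns the task to one centre: "The central randomization method will be performed by the Shanghai University of Traditional Chinese Medicine". It continues: "Block randomization will be used, and the block size will be unknown to the researchers". The ratio is given for the trial as a whole: "Patients will be randomly divided into four groups with the ratio of 1:1:1:1". No stratification factor is named. The section also does not say that a single list serves every hospital.

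The Recruitment section states: "All participants will be recruited in the three hospitals mentioned above through hospital-based advertisements". Under Quality control, acupuncture and sham acupuncture are to be "performed uniformly across the three hospitals, we will carry out centralized trainings twice for these acupuncturists before the trial begins". The same section says that researchers will be trained in the cognitive tests.

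The Statistical analysis section fixes the model for the treatment effects: "The main effect and the interaction effect of the two interventions will be analyzed by 2 × 2 factorial analysis of variance". Hospital is not mentioned there.

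**The concern.** Needling is done by different acupuncturists in three hospitals, and the primary outcome, MoCA, is a scale that a tester administers. Hospital is therefore a plausible source of variation in the outcome. A multi-centre trial normally deals with this by keeping the blocks within hospital, by putting hospital in the model, or by both. The article states neither.

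The two halves of the point do not rest on equally firm ground. On allocation the article is silent. On analysis it makes a positive statement: a 2 × 2 factorial ANOVA has two factors, and here they are acupuncture and herbal medicine. As written, variation between hospitals goes into the residual. At stake are the standard errors of the two main effects and of the interaction.

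**Working it through.** **Plan's own figure.** The only design figure is the total of 240. With 85% against 60%, two-sided 0.05 and 80% power, the two-proportion formula with pooled variance under the null gives

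n = [1.96·√(2·0.725·0.275) + 0.842·√(0.85·0.15 + 0.60·0.40)]² / 0.25² ≈ 48.9, so 49 per arm.

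Dividing by 0.8 for dropout gives 62, against 60 stated. With 60·0.8 = 48 per arm, power is 79.3%. The 240 is thus reproduced closely for group A against group D. It is not in dispute here and serves only as the N below.

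**Inputs.** From the article: 240 patients, four arms at 1:1:1:1, three hospitals. Assumed, because the article does not give them: hospital sizes, block size (4 or 8), and the share r of MoCA variance explained by hospital (5% to 10%).

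**Imbalance if one list serves all hospitals.** Half of the 240 receive real acupuncture. With hospitals arriving in random order, the number X on real acupuncture in a hospital of n patients is hypergeometric:

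Var(X) = n·¼·(240 − n)/239, and the real-minus-sham difference is 2X − n.

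| n | Var(X) | SD of difference | P(difference of 10 or more, either way) |
|---|---|---|---|
| 40 | 40·0.25·200/239 = 8.37 | 5.8 | z = 4.5/2.89 = 1.56, about 0.12 |
| 80 | 80·0.25·160/239 = 13.39 | 7.3 | z = 4.5/3.66 = 1.23, about 0.22 |

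(A difference of 10 means that X is 5 from its mean; 4.5 is this value with continuity correction.) Simulation of 20,000 trials per scenario gives the same 0.12 and 0.22.

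**One list against a list per hospital.** Simulation of 5,000 trials, hospital shares equal or 50/30/20%, block size 4 or 8; worst hospital in each trial:

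| Measure | One central list | List per hospital |
|---|---|---|
| Largest minus smallest arm, mean | 9.4–9.7 | 0.9 (block 4), 1.5 (block 8) |
| Same, 95th percentile | 15 | 1–2 |
| Real minus sham (absolute), mean | 8.3–8.7 | 1.1–1.5 |
| Same, 95th percentile | 16–17 | 2–3 |

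**What this does to the estimate.** Over randomisation these differences average to zero. With one list, a hospital component of the outcome with standard deviation s adds error to a main effect with standard deviation of about 2s/√240 = 0.13s. Any other source of outcome variation acts in the same way, and the ANOVA residual already covers it. This is random error, not bias.

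**Precision lost by leaving hospital out.** The standard error of a main effect is 2σ/√240. With hospital in the model, σ becomes σ√(1 − r), so omitting it multiplies the standard error by 1/√(1 − r):

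- r = 0.05: 1/√0.95 = 1.026, or 2.6% larger, equivalent to 0.05·240 = 12 patients.
- r = 0.10: 1/√0.90 = 1.054, or 5.4% larger, equivalent to 0.10·240 = 24 patients.

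With one list this extra error is real. With blocks kept per hospital, the design has removed most of it from the estimate, but the stated ANOVA still counts it in the residual. The reported standard error is then too large and the test conservative.

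**Cost of including hospital.** Residual degrees of freedom fall from 240 − 4 = 236 to 234. With one list, the expected information lost to imbalance is about 2/239 = 0.8%, or about 2 of 240 patients. Adjustment therefore pays once hospital explains more than about 0.8% of the variance. If it explains nothing, the standard error rises by only about 0.4% (1/√0.992 = 1.004).

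**The case against.** The strongest reply is that the article never says the blocks are unstratified. Central randomisation is compatible with a list per hospital, and an article commonly leaves list structure to the full protocol, and model covariates to the analysis plan. This stands as far as allocation goes: a reader might infer that the trial decided against stratifying, but the text is silent and does not support that. It stands less well for the analysis, where the model is named and its factors are the two interventions.

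It can also be said that the hospitals may not differ. Eligibility criteria are common to all, and Quality control plans two central trainings of acupuncturists and training in the cognitive tests. No section reports a difference between hospitals in testers, education or patient mix, nor labels any of them a general hospital. So the size of any hospital effect is unknown, and r is an assumption. Training reduces such variation, but it neither balances nor adjusts for what remains.

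Finally, a reader might take the imbalance counts as a sign of biased treatment comparisons, or think of 60 against 60. Neither reading holds. Randomisation keeps the contrasts unbiased, and a factorial main effect compares 120 with 120.

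**Conclusion.** The point holds as one of modest size about precision. Three hospitals recruit, no stratification by hospital is stated, and the stated model contains only the two interventions. On either reading of the allocation text, the model is less precise than it could be: by about 2.6% to 5.4% in standard error if hospital explains 5% to 10% of MoCA variance, and by little or nothing if hospital explains little or nothing. The chances of 12% and 22% apply only if one list serves all hospitals, and at the assumed sizes of 40 and 80. The documents do not establish a decision against stratifying, a known difference between hospitals, or bias. The case for the hospital factor does not depend on which reading is right.

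**What to change.** Add hospital as a fixed factor to the 2 × 2 model, keeping both interventions and their interaction. This takes 2 degrees of freedom and one sentence in the protocol.

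State also whether blocks are kept per hospital. If they are not and recruitment has not begun, have the central system hold a separate permuted-block list for each hospital, with undisclosed block sizes that are multiples of 4; this is a setting in the existing system. The Trial status section gives June 2018 as the planned start of recruitment. If patients have already been randomised, leave the allocation as it is and add only the factor.

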### Intervention

During the trial, the participants are permitted to continue their regular medications including lipid-lowering drugs, antihypertensive drugs and drugs not related to the treatment of cognitive impairment. Drugs that may interfere with the efficacy of the study therapies will be banned such as cholinesterase inhibitor, non-steroidal anti-inflammatory drug (NSAID), etc.

Participants in the four groups will receive different treatments of acupuncture and herbal formula. Both the acupuncture and sham acupuncture treatments will be given twice a week for 8 weeks and then once a week for 4 weeks. Each treatment will last 30 min. A total of nine acupoints will be treated in the two therapies, including *Baihui* (DU20), *Shenting* (GV24), *Yintang* (GV29), *Sishencong* (EX-HN1), bilateral *Anmian* (EX-HN22), bilateral *Shenmen* (HT7), bilateral *Sanyinjiao* (SP6), bilateral *Hegu* (LI4), and bilateral *Taichong* (LR3). Participants will wear an eye-mask and lie in the supine position during the treatment. Needling will be performed after a routine skin disinfection. All the acupuncturists are licensed and have 3–5 years of experience in acupuncture treatment. Electrical stimulation will not be used in this trial.

The herbal treatment, YSG, will be given granules daily for 12 weeks, which is composed of 8 weeks of standard-dose followed by 4 weeks of mid-dose. The Chinese herbal formula, YSG, is composed of ten herbs, the main ones are *Rhizoma cyperi* 15 g, *Rhizoma acori tatarinowii* 9 g, *Radix polygalae* 9 g, as well as *Cortex cinnamomi* 3 g. The herbs will be mixed, cooked, filtered, and pressure-spray-dried to form the granules. The mid-dose YSG will contain half of the drug ingredient compared with the standard-dose YSG. All the granules will be packaged in single-dose sachets. Participants will receive individual packaged doses, with each dose to be dissolved in warm water and taken orally twice per day.

Both treatments will be performed by the same researcher. The granules will be provided every 4 weeks in a box; twenty-eight doses per box, three times in total. Participants will receive the study granule after the acupuncture treatment.

To ensure the adherence, the participants will be required to return the box before the new herbal medicine is provided. Participants who are unable to attend the appointment should contact the researchers in advance to reschedule. After all the treatments and assessments are completed, patients in all four groups will receive 400 RMB (about US$58) as a financial subsidy. All patients will, respectively, receive 200 RMB at the end of intervention and another 200 RMB at the end of the follow-up.

#### Group A

Participants in group A will receive acupuncture with YSG treatment. YSG was produced by a medical corporation (Beijing Tcmages Pharmaceutical co., Ltd., China). The real tube-needling (Wuxi Jiajian Medical instruments Co., Ltd., China) method will be used in group A. After insertion of needles, a lifting-thrusting manipulation or rotating manipulation will be applied to achieve a *De-Qi* sensation (a needling sensation of soreness, numbness, heaviness and/or distention). The acupuncture method is shown in Table 1.

**Table 1 Tab1:** Acupuncture method

	Acupuncture treatment	Sham acupuncture treatment
Acupoints	DU20, GV24, GV29, EX-HN1, EX-HN22 (bilateral), HT7 (bilateral), SP6 (bilateral), LI4 (bilateral), LR3 (bilateral)	DU20, GV24, GV29, EX-HN1, EX-HN22 (bilateral), HT7 (bilateral), SP6 (bilateral), LI4 (bilateral), LR3 (bilateral)
Depth of needle insertion	DU20, GV24, GV29, EX-HN1, EX-HN22, HT7: 0.5 body-inches SP6: 1–1.5 body-inches LR3, LI4: 0.5–1 body-inches	No needle insertion
Response sought	*De-Qi* sensation	Without *De-Qi* sensation
Needle stimulation	Manual stimulation: lifting-thrusting manipulation or rotating manipulation will be applied to achieve a *De-Qi* sensation	No needle stimulation
Needle-retention time	Thirty min	Thirty min
Needle type	Stainless steel (0.30 × 25 mm or 0.30 × 4 0 mm; Wuxi Jiajian Medical instruments Co., Ltd., China)	Blunt stainless steel (0.30 × 25 mm or 0.30 × 40 mm; Wuxi Jiajian Medical instruments Co., Ltd., China)
Number of treatment sessions	Twenty treatment sessions in total	Twenty treatment sessions in total
Frequency and duration of treatment sessions	Twice per week for 8 weeks and followed by once a week for 4 weeks	Twice per week for 8 weeks and followed by once a week for 4 weeks
Other components of treatment	YSG or placebo herbal medicine	YSG or placebo herbal medicine

#### Group B

Participants in group B will receive acupuncture with placebo herbal medicine treatment. The placebo herbal medicine will be produced by the same company as YSG. The placebo is made of starch, caramel, coloring, and bitter flavoring, and will be given for 12 weeks in total. The appearance and taste of the placebo will be almost identical to the YSG.

#### Group C

Participants in group C will receive sham acupuncture with YSG treatment. The placebo acupuncture needle we adopt will be able to simulate an acupuncture procedure without penetrating the skin [19]. The patients will feel a pricking sensation when the tip of the blunt needle touches to the skin [20]. Meanwhile, the needle will retract inside the handle and appear to be shortened [20].

#### Group D

Participants in group D will receive sham acupuncture with placebo herbal medicine treatment.

### Outcomes

#### Primary outcome

The Montreal Cognitive Assessment (MoCA) is a one-page, 30-point test administered in 10 min [21]. The MoCA is a brief cognitive screening tool with high sensitivity and specificity for detecting MCI [21]. The current version tests eight cognitive functions: visuospatial functions, executive functions, memory, attention, and concentration, language, calculations, conceptual thinking, and orientation [22]. The Chinese version of the MoCA test is available from the following official website: https://www.mocatest.org/wp-content/uploads/2015/tests-instructions/MoCA-Test-Chinese_Beijing.pdf. Total scores of MoCA ranges from 0 to 30. A score of 25 or below indicates the possibility of cognitive impairment [22].

#### Secondary outcomes

The secondary outcomes refer to the MMSE and ERP.

The Mini-Mental State Examination (MMSE) is one of the most commonly used screening instruments for estimating the severity of cognitive impairment [23]. The MMSE is an 11-question measure that comprises five areas of cognitive function: orientation, registration, attention and calculation, recall, and language [24]. The total score of the MMSE ranges from 0 to 30. For a respondent with a high-school education and above, a score lower than 24 indicates possible cognitive impairment, and for a respondent with only a primary school education or who is illiterate, the cutoff scores are respectively 20 and 17 [25]. A lower score indicates a higher degree of cognitive impairment.

The event-related potential (ERP) is a kind of electrophysiological method with high temporal resolution [26]. ERPs have been used to examine the neurophysiological underpinnings of many conditions including MCI and AD [27]. P300 is one of the ERP components, which have been used to map the neural responses of memory [26]. Several subsequent memory effects, which measured activity differences that predict whether stimuli are later remembered or forgotten, are commonly observed as differences in P300 [28].

#### Adverse events

Adverse events (symptoms or diseases occurring during the trial) will be recorded and assessed at each session of intervention. The adverse events mainly include abnormal gastrointestinal reactions, allergic reactions, dizziness, itching after acupuncture, and other medical conditions. The relevance and severity of the adverse events will be assessed. Whether the participant could continue the treatment or not will be decided according to the assessments.

### Quality control

To ensure the quality of the trial, it will be conducted at three hospitals, and the trial data will be input on the ResMan website in a timely manner. The Clinical Research Center of Drugs of the Shanghai Municipal Hospital of Traditional Chinese Medicine will work as the data monitoring team to identify the existing problems in the project, control the bias, and make the final decision to terminate the trial. A qualified clinical trial expert will be invited to monitor this RCT. Researchers will be trained to ensure the quality of the cognitive tests. Acupuncturists participating in this trial are all certificated physicians with 3–5 years of clinical experience. To ensure that the acupuncture and sham acupuncture treatment are performed uniformly across the three hospitals, we will carry out centralized trainings twice for these acupuncturists before the trial begins.

### Statistical analysis

An intention-to-treat (ITT) analysis will be used in this RCT. Data analyses will be performed with the use of the statistical software SPSS20.0. The baseline characteristics of the participants in the four groups will be dealt with using the chi-squared test and Fisher Exact Test for categorical data and analysis of variance for continuous variables. Intragroup comparisons will be performed via the use of paired *t* test. The main effect and the interaction effect of the two interventions will be analyzed by 2 × 2 factorial analysis of variance. The statistical significance is set at *P* < .05. All the *P* values are two-side.

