## Methods/design

### Setting and design

A multi-sited, patient-assessor-blinded, RCT is designed to evaluate the efficacy and safety of acupuncture and the herbal formula, *Yishen* Granule (YSG), for elderly patients with mild cognitive impairment. Eligible patients will be randomly divided into four groups in a 1:1:1:1 allocation ratio, receiving acupuncture with YSG, acupuncture with placebo herbal medicine, sham acupuncture with YSG, or sham acupuncture with placebo herbal medicine. All the participants will be recruited in Shanghai Municipal Hospital of Traditional Chinese Medicine, Shanghai East Hospital, or Jingan District Hospital of Traditional Chinese Medicine. Written informed consent will be obtained from all patients. The primary outcome is scored by the Montreal Cognitive Assessment (MoCA). The secondary outcomes will be scored by the Mini-Mental State Examination (MMSE) and event-related potential (ERP). All the assessments will be conducted at baseline, and at the eighth and 12th weeks after the intervention starts. The follow-up assessments will be performed with MoCA in the 12th, 24th, and 36th weeks after intervention ends. The flowchart of the study process can be seen in Fig. 1, and the timing of treatment visits and data collection can be seen in Fig. 2 and Additional file 1.

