### Sample size

The calculation of the sample size in this trial was based on the change of the MoCA score. Referring to the related trial published in *BMC Complement Alternative Medicine* [7], 80% of patients with MCI showed an improvement of at least 12.5% on the MoCA score after acupuncture treatment. We assumed the rate to be 80% with one active and one control intervention, 85% with both active interventions and 60% with both control interventions. Under the assumption of a significant level of 0.05, 80% power, and 20% dropout rate, a total of 240 participants should be recruited for this RCT (60 participants in each group with 1:1:1:1 allocation).

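### Within-group paired t tests share the P < .05 threshold with the factorial analysis, although on the plan's own 60% assumption even sham plus placebo is expected to show significant change (minor)

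*Protocol article*

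**What the plan says.** Three places in the protocol article bear on this point.

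- **Statistical analysis, within groups.** "Intragroup comparisons will be performed via the use of paired" t tests. The section sets one significance threshold, P < .05, and adds that all P "values are two-side". The paired tests are not called descriptive, secondary or exploratory, and the section does not say at which visits they will be done.
- **Statistical analysis, between groups.** The next sentence reads: "The main effect and the interaction effect of the two interventions will be analyzed by 2 × 2 factorial analysis of variance". This is the only analysis that the article assigns to the effects of the two interventions.
- **Sample size.** Improvement is taken from a cited trial as a MoCA gain of at least 12.5%. The assumed rates are 80% with one active intervention and "85% with both active interventions and 60% with both control interventions". The other inputs are "a significant level of 0.05, 80% power, and 20% dropout rate", leading to 60 patients per group and 240 in total. No mean or SD of MoCA change is given.

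The MoCA is given at baseline and at weeks 8 and 12 of treatment. After that, "The follow-up assessments will be performed with MoCA in the 12th, 24th, and 36th weeks after intervention ends". That makes six administrations, five of them after baseline.

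**The concern.** A paired t test asks whether the mean change in one arm differs from zero. In a randomised trial that is not the treatment question. Change within an arm combines any treatment effect with retesting on the same instrument, placebo response, regression to the mean and spontaneous recovery. The article's own Discussion cites reversion to normal or near-normal cognition in about 16% of adults with MCI after about a year. It also explains that sham and placebo are there to isolate the specific effects of the two treatments. A test inside one arm cannot do that; only a comparison between randomised arms can.

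The plan's own figures make the problem concrete. If 60% of patients on double control are expected to improve, a significant change from baseline in an active arm says little, because the same result is expected without active treatment. Comparing significance across arms does not help either: a significant result in group A and a non-significant one in group D is not a test of A against D.

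At stake is how the results could be read. With four arms and up to five post-baseline MoCA visits, as many as 4 × 5 = 20 non-randomised P values could stand beside the factorial results at the same threshold.

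**Working it through.** **Inputs from the article.** Two-sided alpha 0.05; 80% power; 20% dropout; improvement rates 85% (A), 80% (B and C) and 60% (D); improvement meaning a MoCA gain of at least 12.5%; 60 patients per group.

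**Inputs assumed, because the article does not give them.** Mean baseline MoCA 16 to 24, SD of change 1.5 to 8 points, roughly normal change.

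**Step 1: reproduce the plan's figure.** Arcsine formula for 85% against 60%:

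- h = 2·asin(√0.85) − 2·asin(√0.60) = 0.574
- n = 2(1.960 + 0.842)² / 0.574² = 47.6, so 48 per arm
- 48 / 0.8 = 60 per group, and 4 × 60 = 240

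The stated 240 is reproduced as a comparison of A with D, so the 60% appears to be a working input to the design. It also gives 48 completers per group.

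**Step 2: what 60% implies for the mean change in group D.** If change is normal and 60% of patients reach 0.125 × baseline, then

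mean change = 0.125 × baseline + 0.253 × SD.

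Example, baseline 20 and SD 3: 2.5 + 0.76 = 3.26 points.

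**Step 3: power of the paired t test in group D.** Noncentrality = (mean / SD) × √48, with 47 degrees of freedom. In the example: (3.26 / 3) × 6.93 = 7.53.

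| Baseline | SD | Mean change | Power in D |
|---|---|---|---|
| 20 | 3 | 3.26 | >0.999 |
| 20 | 5 | 3.77 | 0.999 |
| 20 | 8 | 4.53 | 0.970 |
| 16 | 5 | 3.27 | 0.993 |
| 16 | 8 | 4.03 | 0.927 |
| 24 | 8 | 5.03 | 0.989 |

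Over the whole grid power runs from about 93% to above 99.9%, and it is at least 99% for every SD up to 5. At baseline 20 and SD 2 to 5, the product of the four arm-wise powers (all four groups significant) is above 0.999.

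**Step 4: does the 60% alone force this?** No. A responder rate does not fix the mean. Suppose 60% gain exactly 2.5 points (12.5% of 20) and the other 40% change by −2 on average, with SD 1 among them:

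- mean = 0.6 × 2.5 + 0.4 × (−2) = 0.7
- SD = √(0.24 × 4.5² + 0.4 × 1²) = 2.29
- simulated power with 48 patients: 0.54

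If noise of SD 1 is added to every patient around those two means, power is 0.49. In that noisy version it is 0.96 when the non-improvers average −1, and 0.11 when they average −3.

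**Step 5: a smaller common gain.** Suppose instead that every arm gains 1 point from retesting and nothing else (an illustrative figure with no source in the article). With SD 2.5, 3 or 3.5, each arm is significant with probability 0.77, 0.62 or 0.49. The chance that A is significant and D is not is p(1 − p), that is 0.77 × 0.23 = 0.18, 0.62 × 0.38 = 0.24 or 0.49 × 0.51 = 0.25, although the arms are identical.

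**The case against.** The strongest reply is that the plan does not use the paired tests to judge treatment. The main effects and the interaction are assigned to the factorial ANOVA, and the Discussion states the aim in terms of additive or synergistic effects. No sentence says that a within-group P value will count as evidence of efficacy. This stands. A reader might infer that the sponsor intends to claim efficacy arm by arm, but the article does not support that: it is a risk of later misreading, not a stated intention.

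Second, a reader might infer from the 60% that all four groups are bound to be significant. Step 4 shows that this does not follow. The near-certainty needs an assumed baseline, SD and roughly normal change.

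Third, the two worrying patterns exclude each other. If D is almost sure to be significant, significance in A but not in D is very rare. This also stands: the patterns belong to different assumptions (large gains in Step 3, small ones in Step 5). Neither pattern is informative about treatment.

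Fourth, the 49% to 77% in Step 5 might be read as false-positive rates. They are not. The null hypothesis is zero mean change, and if retesting truly raises the mean by 1 point, rejection is correct. It misleads only if the change is credited to treatment.

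Finally, this is a condensed article, and the ranking of analyses is often left to an analysis plan that is not shown. That explains the missing label. It does not remove the stated choice to test within groups under a single threshold.

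**Conclusion.** The point holds in a limited form and is minor. The article plans within-group significance tests that do not use the randomisation, with nothing to set them apart from the treatment analysis. On its own 60% rate for sham plus placebo, significant change is expected in every arm, group D included: about 93% to above 99.9% with 48 completers. That range rests on a baseline of 16 to 24, an SD of change up to 8 and roughly normal change, all assumed. It could fall to about 50% if the non-improvers lost some 2 points on average.

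The documents do not support the stronger conclusions that significance in every arm is certain or that efficacy will be judged on these tests. The between-group analysis that should carry the efficacy conclusions is already named.

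**What to change.** Replace the sentence on paired t tests with a statement that mean change from baseline and its 95% CI will be reported for each group, descriptively and without P values. Add that every efficacy statement will rest on the between-group contrasts of the factorial model.

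In the same revision, add baseline MoCA to that model as a covariate. This is a second, separate change to the planned ANOVA, but the score is already collected and adjustment should improve precision.

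The cost is a small change of text and the loss of the within-group P values. No new data, visits or patients are needed.
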